# Umbilical cord-derived Wharton’s jelly for treatment of knee osteoarthritis: study protocol for a non-randomized, open-label, multi-center trial

**DOI:** 10.1186/s13018-021-02300-0

**Published:** 2021-02-18

**Keywords:** Umbilical cord, Wharton’s jelly, Knee osteoarthritis, Regenerative medicine, Biologics, Clinical trial, Extracellular vesicles, Exosomes, Growth factors, Hyaluronic acid

## Abstract

**Background:**

Osteoarthritis (OA) is the most common joint disorder in the USA, and knee OA has the highest prevalence. Inflammation and decrease in vascularization are key factors in the degeneration of articular cartilage and the associated pain and decrease in function. To combat this process, the use of biologics including umbilical cord-derived Wharton’s Jelly (UC-derived WJ) has grown. UC-derived WJ contains large quantities of regenerative factors, including growth factors (GFs), cytokines (CKs), hyaluronic acid (HA), and extracellular vesicles (EVs). The proposed study evaluates the safety and efficacy of intraarticular injection of UC-derived WJ for treatment of knee OA symptoms.

**Methods and analysis:**

This is a non-randomized, open-label, multi-center, prospective study in which the safety and efficacy of intraarticular UC-derived WJ in patients suffering from grade II/III OA will be assessed. Twelve patients with grade II/III OA who meet the inclusion and exclusion criteria will be recruited for this study which will be conducted at up to two sites within the USA. The participants will be followed for 1 s. Participants will be assessed using the Numeric Pain Rating Scale (NPRS), Knee Injury and Osteoarthritis Outcome Score (KOOS), 36-item short form survey (SF-36), Single Assessment Numeric Evaluation (SANE), physical exams, plain radiography, and Magnetic Resonance Observation of Cartilage Repair Tissue (MOCART) score for improvements in pain, satisfaction, function, and cartilage regeneration.

**Discussion:**

This prospective study will contribute to the limited amount of data on UC-derived WJ, particularly with regard to its safety and efficacy. The outcomes from this study will also lay the groundwork for a large placebo-controlled trial of intraarticular UC-derived WJ for symptomatic knee OA.

**Trial registration:**

ClinicalTrials.gov NCT04719793. Registered on 22 January 2021

## Background

Osteoarthritis (OA) affects approximately 30 million American adults aged 25–74 years, making it the most common joint disorder in the USA [1]. OA is characterized by degeneration of articular cartilage and secondary osteogenesis, with the earliest pathological changes seen in the articular cartilage [2]. Larger weight-bearing joints such as knees, hips, and the facet joints of the spine are OA most frequent targets [3, 4]. Of all the joints it affects, knee OA is the most prevalent with the number of adults suffering expected to reach 67 million by 2030 [5, 6].

While knee OA is a prominent cause of disability in adults, there is no clear etiology to explain its pathology. Knee OA has been suggested to be related to age, obesity, joint trauma, mechanical damage, gender, and other factors [7, 8]. The pathology of knee OA may be linked to degenerative lesions in cartilage secondary to inflammation associated with hyperplasia and chondrocyte apoptosis [9, 10]. Increasing age is linked to a reduction in subchondral blood vessels resulting in cartilage related physiological and biochemical anomalies [11]. Additionally, the inability of long-chain hyaluronic acid and polyglucose to generate chondrocytes results in local softening of articular cartilage, loss of elasticity, wear, and structural damage. This pathological process results in secondary joint fibrosis, stiffness, pain, and decreased function; leading to a poor quality of life [8, 11]. Knee OA treatment aims to decrease or eradicate pain, enhance or restore joint function, rectify any morphological or alignment defects, and improve quality of life.

Currently, there are various treatment options used in clinical practice to manage knee OA, including activity modification, physical therapy, pharmacological agents such as NSAIDs, corticosteroids, viscosupplementation, and narcotics. These treatment modalities have shown variable and limited clinical benefits and have potential side effects. When conservative measures fail, total knee replacement is usually recommended [12–20]. While total knee replacement (TKR) surgeries typically result in decreased pain, improved joint function, and reduced disability; complications, such as infection, persistent pain, and loss of motion may occur, and may require revision surgery. In addition, outcomes after TKR surgeries for patients with less severe knee OA (grades II and III) are worse compared to patients with grade IV OA (on Kellgren-Lawrence scale) [21–23]. An additional goal of non-operative therapy is to delay or even avoid surgical intervention. Decreasing the number of TKR surgeries will result in fewer revision surgeries, potentially saving patients from multiple costly surgeries and extensive rehabilitations, and decreasing the healthcare burden [21].

Over the last decade, the use of biologics for regenerative medicine applications has gained popularity [24–30]. Despite their increased use, there are inadequate studies evaluating the amount of growth factors (GFs), cytokines (CKs), hyaluronic acid (HA), and extracellular vesicles (EVs) including exosomes present in these products. Specifically, there is limited or no clinical literature assessing the safety and efficacy of UC-derived WJ products. We formulated an UC-derived WJ product and analyzed it for the presence of these factors. The vital elements of regenerative medicine, namely GFs, CKs, HA, and EVs, are all present in large quantities in the formulated WJ [31]. This study allowed us to characterize this novel WJ formulation prior to conducting clinical trials to determine the safety and efficacy—for regenerative medicine applications.

The goal of the proposed study is to evaluate the safety and efficacy of intraarticular injection of UC-derived WJ for treatment of knee OA symptoms. We hypothesize that the intraarticular injection of WJ is safe, and participants will show an improvement in their overall satisfaction, Numeric Pain Rating Scale (NPRS), Knee Injury and Osteoarthritis Outcome Score (KOOS), and cartilage formation over a period of 1 year compared to the baseline visit. Our null hypothesis is that there is no difference between baseline and after-treatment time-points over a period of 1 year.

## Methods and analysis

This study protocol is reported in accordance with the Standard Protocol Items- Recommendations for Intervention Trials (SPIRIT) criteria [31, 32]. The complete SPIRIT checklist can be found in Supplementary data.

### Study design

Twelve patients with grade II/III OA who meet the inclusion and exclusion criteria will be recruited for this non-randomized, open label, multi-center, prospective study. The study will be conducted at two sites within the USA, and the patients will be followed for 1 year, with an expected duration of 15 months (Figs. 1 and 2). Figure 2 depicts the schedule for enrolment, intervention and assessment according to the SPIRIT guidelines.

**Fig. 1 Fig1:**
[figure not shown]
Summary of trial design

**Fig. 2 Fig2:**
[figure not shown]
Standard protocol items: recommendations for interventional trials (SPIRIT) flowchart

### Inclusion criteria

Patients who are 18 years or older with a body mass index (BMI) of < 40 kg/m^2^ and a diagnosis of mild to moderate (grade II/III) OA in only one knee on the KL grading scale will be recruited. Patients must also meet the following criteria:
Pain score of 4 or more on the NPRSWilling and capable of giving written informed consent to participateWilling and capable of complying with study-related requirements, procedures, and visitsFemale patients must be abstinent, surgically sterilized, or postmenopausalPremenopausal females with negative pregnancy test, and who does not anticipate pregnancy and will actively practice an accepted contraceptive method for a duration of the studyMales with premenopausal female partners will take contraceptive measures for the duration of the study

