### Exclusion criteria

Patients who have taken any pain medications including non-steroidal anti-inflammatory drugs (except acetaminophen) within 15 days of the study injection date or that regularly use anticoagulants, have a substance abuse history and/or fail to agree not to take any knee-symptom modifying drugs during the course of the study without proper reporting to the site PI and study team will not be eligible to participate. Patients must also not meet the following criteria:
Evidence of pathological knee laxity or instability on physical examHistory of intraarticular injection of any drug including corticosteroids or viscosupplementation in the index knee within the last 3 monthsKnee surgery on the index knee within the last 6 monthsTraumatic injury to the index knee within the last 3 monthsPlanned elective surgery during the course of the studyOrgan or hematologic transplantation history, rheumatoid arthritis, or other autoimmune disordersImmunosuppressive medication/treatmentDiagnosis of non-basal cell carcinoma within the last 5 yearsA knee infection or use of antibiotics for a knee infection within the last 3 monthsParticipation in another clinical trial or treatment with any investigational product within the last 30 days prior to inclusionFemale patients who are breast feeding or are pregnant or desire to be pregnant during the course of the studyContraindications to plain radiography or MRI imagingSerious neurological, psychological or psychiatric disordersOther medical conditions determined by the site principal investigator as interfering with the studyAn injury or disability claim under current litigation or pending or approved workers’ compensation claim

Participants will have the opportunity to voluntarily withdraw from the study at any time without any sanction or affect to their access to other treatments. The participation of a patient in the study may be terminated if continued participation is not in the subject’s best interest based on standard medical practice by the PI. Any participant with any adverse events (AEs) regardless of whether it is related to the treatment can withdraw voluntarily from the study.

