#### Secondary endpoints

To assess change in patient-reported outcome measures, NPRS and KOOS, from baseline to various follow-up time points.To assess cartilage formation via MOCART at the 1-year time point and compare if from baseline.To assess patient satisfaction using SF-36, 7-point Likert scale and Single Assessment Numeric Evaluation (SANE).

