### Sample size and statistical analysis

Descriptive statistics will be computed for all study variables. Continuous variables will be described with measures of central tendency (mean, median) and dispersion (range, standard deviation). Categorical variables will be summarized as frequencies and percentages. Comparisons between categorical variables will be compared with the chi-square test; continuous variables will be compared with Student’s *t* test or non-parametric equivalents. Paired continuous data will be assessed with a paired *t* test or Wilcoxon signed rank test, depending on distribution. Paired categorical data will be assessed with McNemar’s test. For the longitudinal data, a mixed-model repeated measures analysis will be used to examine the between subject factors and the within subject factor of time (baseline, visit 1, visit 2, etc.), as well as their interaction, on the outcome variables of interest. Post hoc tests with corrections for multiple comparisons will be run to determine where significance lies. *P* values < 0.05 will be considered statically significant.

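### Three exclusion windows cover only the index knee and the other knee's required status is unclear, so recovery of the other knee may be read as improvement after the injection

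*Protocol article*

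**What the plan says.** All references are to the Protocol article.

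- **Inclusion criteria.** Patients with a "diagnosis of mild to moderate (grade II/III) OA in only one knee on the KL grading scale will be recruited". No separate condition is set for the other knee. The same section requires an NPRS score of at least 4 and names no knee for it.
- **Exclusion criteria.** Three time windows are each restricted to the index knee: intraarticular injection (3 months), knee surgery (6 months) and traumatic injury (3 months). Other items in the list carry no such restriction: knee infection, knee laxity or instability, planned elective surgery, recent pain medication, and conditions that the site investigator judges to interfere.
- **Study design.** "Twelve patients with grade II/III OA who meet the inclusion and exclusion criteria will be recruited", in a single open-label cohort.
- **Background.** "Our null hypothesis is that there is no difference between baseline and after-treatment time-points over a period of 1 year".
- **Secondary endpoints.** "To assess change in patient-reported outcome measures, NPRS and KOOS, from baseline to various follow-up time points", together with MOCART at 1 year and satisfaction measured by SF-36, a 7-point Likert scale and SANE. The primary endpoint is safety.

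**The concern.** Each patient serves as his or her own control over 1 year. Such a comparison credits the treatment with anything that changes in the patient over that year, so eligibility rules are the main protection against changes that were already under way. The windows for injection, surgery and trauma give that protection for the treated knee. They do not give it for the other knee, and a patient can be on a recovery path there too.

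Pain and general health do not separate cleanly by knee unless the form asks for one knee. A patient who enters soon after an operation on or injury to the other knee may report less pain and better general health a year later whether or not the product works. The entry threshold has the same weakness: as worded, pain from the other knee could qualify a patient. The Discussion says positive results would lay the foundation for a placebo-controlled trial, so a distorted change estimate could carry forward.

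**Working it through.** The plan gives no figure to reproduce. It states N = 12 without an effect size, standard deviation or power, and the point does not depend on these. The check is a reading of the rules, followed by one line of arithmetic.

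**Step 1: what the inclusion rule requires of the other knee.** There are two readings.

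- Unilateral OA: one knee has OA, and it is grade II/III. The other knee has none.
- Literal: grade II/III is present in one knee only, and other grades in the other knee are not mentioned.

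The first is the natural reading. The second is possible, so the rule is ambiguous, but the text does not deliberately admit bilateral disease. Neither reading says whether a replaced other knee counts as a knee with OA.

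**Step 2: which exclusions reach past events in the other knee.** Take the unilateral reading and an other knee without OA.

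| Event in the other knee | Exclusion that names it | Reaches the other knee? |
|---|---|---|
| Injection in the last 3 months | Injection window | No, index knee only |
| Surgery in the last 6 months | Surgery window | No, index knee only |
| Trauma in the last 3 months | Trauma window | No, index knee only |
| Infection in the last 3 months | Infection item | Yes, as worded |
| Surgery still to come | Planned elective surgery | Yes |

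The gap is therefore present even on the reading most favourable to the plan. For example, a patient 2 months after surgery on the other knee is inside the 6-month window, but that window does not apply.

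**Step 3: which outcomes can carry the other knee's course.**

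- NPRS: exposed as worded, since no knee is named.
- SF-36: a general-health measure, so exposed wherever it is compared with baseline. The Assessment points section lists it by name only at baseline. The schedule figure is not shown.
- KOOS and SANE: not directly exposed if completed for the index knee. The article does not say which knee.
- MOCART: an imaging score of cartilage, so it does not carry the other knee's pain or recovery.

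**Step 4: size.** Let k patients have a change score displaced by b points because of the other knee. If all 12 are analysed with equal weight, the mean change shifts by

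k × b / 12.

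Neither k nor b is in the documents. With assumed values on NPRS:

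- k = 1, b = 2: 1 × 2 / 12 = 0.17 points
- k = 1, b = 4: 1 × 4 / 12 = 0.33 points
- k = 3, b = 2: 3 × 2 / 12 = 0.50 points
- k = 3, b = 4: 3 × 4 / 12 = 1.00 point

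Here b is only the part of the change caused by the other knee. If a patient's NPRS falls by 4 points and would have fallen by 2 anyway, then b = 2 and the shift is 0.17, not 0.33. The sign of b is also open: recovery of the other knee flatters the product, and deterioration does the reverse.

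**The case against.** The strongest reply has four parts.

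1. **The inclusion rule already means unilateral OA.** This stands as the natural reading. A reader might infer from the literal wording that patients with grade IV disease in the other knee are admitted. The document does not support that: the wording can be misread, but it does not grant entry. The reply does not cover an other knee without OA that was recently operated on, injured or injected.

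2. **Other exclusions remove many of these patients.** The list also bars "Patients who have taken any pain medications including non-steroidal anti-inflammatory drugs (except acetaminophen) within 15 days of the study injection date", any planned elective surgery, and conditions the site investigator considers to interfere. This stands in part. Patients still taking analgesics other than acetaminophen would be removed, and an injection into the other knee a week before entry might be caught as pain medication. The pain-medication rule looks back only 15 days, against 3 and 6 months for the windows. The planned-surgery rule does not reach past surgery, and discretion may be used differently at two sites.

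3. **The forms or the full protocol may name the knee.** This stands for NPRS, KOOS and SANE as outcomes. The article condenses a longer document, so silence on the form's wording is not an error in itself. It does not answer the three windows, where the article states the laterality and restricts it to the index knee.

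4. **Limiting the windows to the treated joint is a coherent choice, and the lack of a comparator is openly stated.** Both are true. Rewording eligibility will not turn an uncontrolled study into a controlled one. It does remove one avoidable source of change at little cost.

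**Conclusion.** The point holds as a modest one. Three windows are expressly limited to the index knee, and the inclusion rule does not settle the other knee's status. Patients recovering from recent surgery, replacement, trauma or injection of the other knee may therefore enter, and their recovery may be read as improvement after the injection, chiefly on NPRS and SF-36.

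The size cannot be derived from the documents. On assumed values it is 0.17 to 0.33 NPRS points in the mean for one affected patient and 0.50 to 1.00 for three, in either direction. This assumes that all 12 patients are analysed with equal weight.

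Two stronger inferences are not supported. One is that the efficacy results will be inflated: how many such patients would enter is unknown, some would be removed by other exclusions, and the effect can go either way. The other is that the trial's main conclusion is at stake: the primary endpoint is safety, whereas this point concerns secondary, baseline-referenced outcomes, and not all of those equally.

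**What to change.** - In the Exclusion criteria, apply the existing 3-month injection, 6-month surgery and 3-month trauma windows to either knee. No new threshold is needed.
- In the Inclusion criteria, state that the index knee has KL grade II/III OA and that the other knee has no OA of any grade. Say explicitly how a replaced other knee is treated.
- State that the NPRS entry score of at least 4 refers to the index knee. If the case report forms do not already do so, have NPRS, KOOS and SANE name the index knee as well.

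The cost is a few changes of wording and a slightly smaller pool of eligible patients for a 12-patient study. The design and analysis do not change.

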### Exclusion criteria

Patients who have taken any pain medications including non-steroidal anti-inflammatory drugs (except acetaminophen) within 15 days of the study injection date or that regularly use anticoagulants, have a substance abuse history and/or fail to agree not to take any knee-symptom modifying drugs during the course of the study without proper reporting to the site PI and study team will not be eligible to participate. Patients must also not meet the following criteria:
Evidence of pathological knee laxity or instability on physical examHistory of intraarticular injection of any drug including corticosteroids or viscosupplementation in the index knee within the last 3 monthsKnee surgery on the index knee within the last 6 monthsTraumatic injury to the index knee within the last 3 monthsPlanned elective surgery during the course of the studyOrgan or hematologic transplantation history, rheumatoid arthritis, or other autoimmune disordersImmunosuppressive medication/treatmentDiagnosis of non-basal cell carcinoma within the last 5 yearsA knee infection or use of antibiotics for a knee infection within the last 3 monthsParticipation in another clinical trial or treatment with any investigational product within the last 30 days prior to inclusionFemale patients who are breast feeding or are pregnant or desire to be pregnant during the course of the studyContraindications to plain radiography or MRI imagingSerious neurological, psychological or psychiatric disordersOther medical conditions determined by the site principal investigator as interfering with the studyAn injury or disability claim under current litigation or pending or approved workers’ compensation claim

Participants will have the opportunity to voluntarily withdraw from the study at any time without any sanction or affect to their access to other treatments. The participation of a patient in the study may be terminated if continued participation is not in the subject’s best interest based on standard medical practice by the PI. Any participant with any adverse events (AEs) regardless of whether it is related to the treatment can withdraw voluntarily from the study.

### Study intervention

After patients are determined to be eligible for the study during visit 1 (preliminary/baseline), they will receive an intraarticular injection of UC-derived WJ (GeneXSTEM^TM^) by the site PI during Visit 2.1 (procedure).

### Assessment points

Assessments for the study period will start at visit 1 (preliminary/baseline) which includes a thorough review of the patient’s inclusion/exclusion criteria and proper documentation of the informed consent form prior to participation. Once these steps are met, participant’s demographic information, medical history, and baseline case report forms (CRFs) such as NPRS, KOOS, 36-item short-form survey (SF-36), and Single Assessment Numeric Evaluation (SANE) will be collected. Baseline plain radiography (Standing AP, Flexion PA (Rosenberg method), Lateral, and Merchant views) for OA grading using the KL scale will be obtained. Participants will also undergo a T2-weighted MRI and receive a Magnetic Resonance Observation of Cartilage Repair Tissue (MOCART) score. Additionally, a comprehensive metabolic profile, liver function tests, complete blood count, markers of inflammation (C-reactive protein, erythrocyte sedimentation rate), T,B and NK cell lymphocyte subsets, and serum IgG, IgA, IgM, and IgE levels will be collected. At visit 2.2, immediately after the injection procedure, and at visits 3 (24-h follow-up) and 4 (48-h follow-up), NPRS will be collected. During visits 5 (1-week follow-up) and 6 (6-week follow-up), CRFs (NPRS, KOOS, 7-point Likert scale, and SANE) will be collected. Participants will also undergo a PE and have their comprehensive metabolic profile, liver function tests, complete blood count, markers of inflammation (C-reactive protein, erythrocyte sedimentation rate), T,B and NK cell lymphocyte subsets, and serum IgG, IgA, IgM, and IgE levels collected. During visits 7 (3-month follow-up) and 8 (6-month follow-up), participants will undergo the same process as well as have plain radiographs (standing AP, flexion PA (Rosenberg method), lateral and merchant views) taken. During the participants’ final visit, visit 9 (1-year follow-up), the same process as in visits 7 and 8 will be undertaken with an additional T2-weighted MRI for a MOCART score. Participants will have opportunities to report any AEs at each visit or at any time during the study.

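### The visit-by-visit text collects SF-36 at baseline only, although SF-36 is named as an instrument of a secondary endpoint

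*Protocol article*

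**What the plan says.** All references are to the protocol article.

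- **Secondary endpoints.** The third endpoint reads "To assess patient satisfaction using SF-36, 7-point Likert scale and Single Assessment Numeric Evaluation (SANE", so SF-36 is one of three named instruments.
- **Abstract, Methods and analysis.** SF-36 is among the tools by which improvement in participants is to be assessed.
- **Assessment points, visit 1.** "baseline case report forms (CRFs) such as NPRS, KOOS, 36-item short-form survey (SF-36), and Single Assessment Numeric Evaluation (SANE) will be collected".
- **Assessment points, visits 2.2, 3 and 4.** Only the pain scale is taken, immediately after the injection and then "at visits 3 (24-h follow-up) and 4 (48-h follow-up), NPRS will be collected".
- **Assessment points, visits 5 and 6 (1 week, 6 weeks).** "CRFs (NPRS, KOOS, 7-point Likert scale, and SANE) will be collected".
- **Assessment points, visits 7 and 8 (3 and 6 months).** "participants will undergo the same process as well as have plain radiographs".
- **Assessment points, visit 9 (1 year).** "the same process as in visits 7 and 8 will be undertaken with an additional T2-weighted MRI for a MOCART score".
- **Background, hypothesis.** It is expected that "participants will show an improvement in their overall satisfaction", among other outcomes, "over a period of 1 year compared to the baseline visit". The null hypothesis likewise sets baseline against the time points after treatment.

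The study has one arm. Sample size and statistical analysis provides paired tests and a repeated-measures mixed model with time as the within-subject factor.

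**The concern.** An outcome instrument measured once, before treatment, carries no information about treatment. With no control group, the only efficacy contrast is each patient's later value against the baseline value. If sites follow the Assessment points text, SF-36 will have a baseline value and nothing after it. No paired test can be run, the mixed model has a single time point, and even a plain description of post-treatment status is impossible.

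The endpoint section and the abstract both rely on SF-36, so the article contradicts itself on whether follow-up values will exist. A questionnaire not given at its visit cannot be recovered afterwards. The mismatch therefore needs to be settled before follow-up begins.

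**Working it through.** No sample size, power or error rate is involved. The check is a count of instruments by visit, set against the endpoint.

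**Step 1. Instruments named at each visit (Assessment points).**

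| Visit | NPRS | KOOS | SANE | Likert | SF-36 |
|---|---|---|---|---|---|
| 1 (baseline) | yes | yes | yes | not named | yes |
| 2.2, 3, 4 | yes | no | no | no | no |
| 5, 6 | yes | yes | yes | yes | no |
| 7, 8 | yes | yes | yes | yes | no |
| 9 | yes | yes | yes | yes | no |

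**Step 2. What the repeated process at visits 7 to 9 refers to.** Could it mean the baseline process, which includes SF-36? The text argues against that. Visit 1 already includes radiographs and MRI. Visits 7 and 8 are described as the repeated process with radiographs on top, and visit 9 as that process with MRI on top. These additions make sense only if the process being repeated has no imaging, which is that of visits 5 and 6. The questionnaire list carried forward is therefore the one without SF-36.

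**Step 3. Choice of denominator.** Visits 2.2, 3 and 4 collect NPRS only, so no other questionnaire is expected there. The relevant follow-up visits are 5, 6, 7, 8 and 9, which makes five.

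**Step 4. Counts for the three instruments of the satisfaction endpoint.**

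| Instrument | Named at baseline | Named at follow-up |
|---|---|---|
| SF-36 | 1 | 0 of 5 |
| SANE | 1 | 5 of 5 |
| 7-point Likert | 0 | 5 of 5 |

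**Step 5. Data available with 12 patients and complete follow-up.**

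- SF-36 post-treatment values: 12 × 0 = 0, so there are no baseline-to-follow-up pairs.
- SANE pairs: 12 × 5 = 60.
- Likert post-treatment ratings: 12 × 5 = 60.

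**Step 6. Against the endpoint.** SANE can be analysed as change from baseline. Likert can be analysed as a rating after treatment. SF-36 can be analysed in neither way.

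**The case against.** The strongest counter-argument is that the article condenses a fuller protocol, and that the section Study design points to Fig. 2 for the assessment schedule. That figure is not available here. Because the abstract lists SF-36 among the tools for improvement, follow-up collection was probably intended, and the prose may simply have dropped it. This limits what can be claimed. The text shows that no follow-up SF-36 is named; it does not show that none is scheduled anywhere. The inconsistency remains either way: if Fig. 2 lists SF-36 at follow-up, the figure and the text disagree and a site could follow either.

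A reader might infer more from these passages. The documents do not support the following readings.

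- **That the Likert scale is equally defective because it has no baseline.** The first two secondary endpoints refer to baseline; the satisfaction endpoint does not. A rating given after treatment at five visits can inform it. The Background hypothesis does compare satisfaction with baseline, but it does not say which instrument carries that comparison. The visit 1 list is also introduced as examples, so a baseline Likert is not strictly excluded. That openness does not rescue SF-36, because the follow-up list is closed.
- **That satisfaction would rest on SANE alone.** The Likert ratings remain available.
- **That a quality-of-life hypothesis fails.** The Background hypothesis covers satisfaction, NPRS, KOOS and cartilage formation. Quality of life is an expectation in the Discussion, and nothing assigns SF-36 to it.
- **That SF-36 is mislabelled as a satisfaction measure.** The article does not describe its content, so that point would rest on outside knowledge.

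**Conclusion.** The inconsistency stands for SF-36. The Assessment points text names it at baseline and at 0 of 5 relevant follow-up visits, while the Secondary endpoints section and the abstract depend on it. Followed as written, 0 of 12 patients would have a post-treatment SF-36 value, and the instrument could not contribute to its endpoint.

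This rests on two assumptions: that the repeated process at visits 7 to 9 is that of visits 5 and 6, which the wording supports, and that the prose schedule governs what is collected, which cannot be checked without Fig. 2.

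Severity is moderate. The primary endpoint is safety. NPRS, KOOS, MOCART and SANE each have baseline and follow-up assessments, and one instrument of one secondary endpoint is affected.

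**What to change.** Either of two changes would resolve it.

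1. **Keep SF-36 in the endpoint.** Add it to the follow-up CRF list, at minimum at visit 9, preferably at visits 7, 8 and 9, and state that it is analysed as change from baseline.
2. **Remove SF-36 from the satisfaction endpoint** and from the abstract's list of tools for assessing improvement.

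In both cases, bring the abstract, Assessment points, Secondary endpoints and Fig. 2 into agreement. The Likert schedule needs no change; one sentence stating that it is summarised as a follow-up-only rating would prevent misreading.

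The cost of the first option is a short amendment and one extra self-completed questionnaire: 12 × 1 = 12 forms at visit 9 only, or 12 × 3 = 36 forms at visits 7 to 9. The second option costs only the edit, but leaves the baseline SF-36 without an outcome use.
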